### Intervention and control conditions

#### Whole-family intervention: StrongerTogether

Intervention characteristics are reported in accordance with the template for intervention description and replication (TIDieR) checklist (Hoffmann et al., 2014). StrongerTogether is a modular, whole-family intervention addressing multiple interconnected family challenges simultaneously. It is positioned as a Level 3 intervention on the IASC MHPSS pyramid,^1^ providing focused, non-specialised mental health support for individual families with psychological distress (IASC, 2007). Non-specialised services rely on task-sharing, an evidence-based approach involving the delivery of mental health services by trained providers who do not have specialised or formal mental health training, improving accessibility (Kazdin, 2019; Raviola et al., 2019).

For each family, the intervention is delivered to at least one caregiver and all adolescents aged between 10 and 17 years. It comprises seven core sessions (including six content-specific sessions and a collaborative ‘transition’ session) addressing family roles, communication, problem-solving and future planning, followed by four optional modules of up to four sessions each covering parenting, caregiver mental health, disagreements and financial literacy, as needed. Session content is manualized, a detailed overview of which can be found in Table 1. Sessions take place weekly at a community centre and are delivered by one non-specialist facilitator face-to-face with individual families, with the support of an assistant to coordinate logistics and provide activities for younger children who may attend but not engage in the entire session. Each session involves a 90-min guided activity or discussion with the entire family, followed by a 30-min discussion with caregivers alone to consolidate the information and support them in their role to implement the strategies. To facilitate home practice and sharing of content with non-attending family members, session content is summarised and provided to families through simple, illustrated handouts and audio-recordings created by the StrongerTogether master trainer to accommodate varying literacy levels.

**Table 1. tab1:** Module content and aims

Central family intervention module		Number of sessions
Module	Aims	
1 Our family story	Family develops joint understanding of challenges, goals and strengths of the family Family develops joint understanding of roles and responsibilities Caregivers are encouraged to work together as a team	7
2 How our family wants to be	Family develops a joint understanding of challenges, goals, and strengths of the family Family understands each other and build empathy	
3 Managing difficult feelings and helping each other	Family members build awareness of feelings experienced by themselves and others Family builds skills in grounding and stepping back from thoughts to help them manage difficult thoughts and feelings Family learns how to practice good self-care for positive well-being	
4 Communicating well to support each other	Family understands their common barriers to positive communication Family builds skills in positive communication, including good listening, and expressing themselves	
5 Managing our problems together	Family identifies common problems they are facing Family learns and applies the Stop Think Go problem management steps to their problems	
6 Managing problems when we do not all agree	Family discusses strengths, roles and responsibilities in the family Family identifies common sources of conflict Family learns and applies the Stop Think Go problem-solving steps to problems involving disagreements between family members	
7 Reviewing where we started and where we want to go in the future	Family reviews content learned in sessions Family reviews home practice of strategies and troubleshoots any challenges they have faced Family makes a plan for the future, maintaining progress made through these sessions Facilitator collaboratively determines with caregivers whether they will complete additional modules	

While facilitators are not mental health specialists, they will be selected based on past experience conducting MHPSS activities and working with children, adults and families in the community. All facilitators receive 10 days of training following a structured curriculum introducing core and advanced module content, facilitation techniques, psychological first aid, child safeguarding, ethics and confidentiality and competencies for working with families. Training workshops are conducted by a local experienced MHPSS supervisor. The supervisor provides weekly group supervision sessions to facilitators, covering challenges and successes during implementation, facilitator competencies, management of adverse events and referrals and self-care techniques.

#### Enhanced treatment as usual (ETAU)

The control condition will be an ETAU consisting of one 30–45 min session comprising a structured, family psychoeducation session delivered by a non-specialist facilitator to the participating caregivers and index adolescent. The scripted session consists of (1) sharing the screening results with the family; (2) discussing common and simple self-care strategies to manage distress; and (3) providing information about available MHPSS, caregiving and financial literacy resources and services. The ETAU will be delivered by non-specialist facilitators, who are different from the StrongerTogether facilitators and who receive a separate 1-day training on the delivery of the psychoeducation session.

### Participants

#### Sample population

Participants in the study will be forcibly displaced and host families living in three districts in East Amman, Jordan, that are vulnerable due to a combination of mental health, family and economic factors. For the purposes of this study, we use the term ‘forcibly displaced’ to refer to refugees, asylum seekers and individuals and families of varying legal status who have left their country of origin and are living in Jordan. Families can be of any size or composition (*i.e.*, single-headed, dual-headed and mixed generations), provided there is a legal guardian able to provide consent and take part in the intervention and study. Sampling will be conducted using a community-based case detection and screening approach to ensure that we recruit families most in need of focused mental health support.

#### Participant inclusion/exclusion criteria

Families are eligible to participate in the study if they have at least one child aged 10–17 years and are experiencing two or more psychosocial challenges (where condition A and/or B exists alongside at least one condition from C to E). A brief screening interview will be used to assess the family’s eligibility for the intervention, including:At least one caregiver has mental health challenges;At least one child has mental health challenges;Family relationship challenges causing significant distress or impairment;Caregiver parenting challenges causing significant distress or impairment; orFamily financial stress.

The screening tool will also include two questions to assess the risk of harm through participation.

For a family to participate, all caregivers must provide consent, and at least one child aged 10–17 years must assent to take part. Participants will be excluded from the study if any member of the family:Do not consent or assent;Indicate safety concerns or reluctance to take part in a whole-family programme during screening;Are unaccompanied minors or children who are married (due to guardian consent challenges);Have severe psychiatric, substance abuse or other conditions requiring specialist services (assessed through elevated scores on screening tools);Have a severe disability impacting participation that cannot be overcome with reasonable accommodation, thereby requiring specialist services; orAny family member already receiving Level 3 focused MHPSS (*i.e.*, more targeted care for children or adults with higher levels of distress; for example, those that screened positive on a symptom scale) or Level 4 specialist mental health interventions (IASC, 2007).

Cases requiring specialised services will be referred to the appropriate actors in each location, as this Level 3 intervention is not suitable for severe mental health conditions or protection concerns requiring specialist support.

#### Sample size

The sample size calculation was powered for the sequential dual outcomes approach. Assuming a statistical significance level of 5% with an intra-cluster correlation coefficient of 0.02 and a two-tailed test with 0.85 power, a total sample of 440 index adolescents and 440 caregivers is required (220 per group) to detect a minimum effect size of *d* = 0.15 for any of the three upstream primary outcomes (family functioning, parenting practices or caregiver mental health) (Brown et al., 2022, 2024). This is based on conservative estimates consistent with our previous trials with similar populations (Brown et al., 2022) and the feasibility study (Brown et al., 2024). To account for an anticipated 20% attrition rate due to contextual challenges frequently encountered in humanitarian settings, as well as sub-analyses based on family composition and uptake of advanced modules, the study will aim to recruit between 550–600 index adolescents and their families.^2^

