#### Primary effectiveness hypotheses

StrongerTogether will demonstrate effectiveness through sequential testing of dual pathways:H1 (upstream mechanisms): Families receiving StrongerTogether will show significantly greater improvements in at least one upstream determinant (family functioning, parenting practices or caregiver mental health) compared to enhanced treatment as usual (ETAU) families at endline (T2).H2 (direct effects in high-need families): Among families with adolescents showing elevated baseline distress (emotional and/or behavioural difficulties), the intervention will demonstrate superior effectiveness in reducing adolescent distress compared to ETAU at endline (T2).H3 (moderation effect on downstream outcome): The intervention will strengthen the protective relationship between upstream improvements and adolescent mental health, such that treatment families demonstrate greater child mental health benefits from upstream improvements in family functioning, parenting practices or caregiver mental health compared to control families at endline (T2) and follow-up (T3).

The study is fully powered to test H1 (power = 0.85). H2 and H3 are positioned as exploratory analyses, given limitations regarding sample size (see below for sample size calculation).

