### Trial design

The study is a single masked, two-arm RCT with an embedded qualitative process evaluation. Families will be randomised to the intervention or ETAU arms in a 1:1 allocation ratio. Outcomes will be assessed at baseline prior to randomisation (T0), at midline after the completion of core sessions (T1), at endline after the completion of advanced modules (T2, primary time point) and at follow-up 6 months after endline (T3).

The trial employs a sequential, dual outcomes approach to establish effectiveness through multiple pathways comparing treatment *versus* control conditions: (1) upstream improvements in family functioning, parenting practices or caregiver mental health in the full sample; (2) direct improvements in mental health in high-distress adolescents; or (3) enhanced protective effects of upstream improvements on adolescent mental health. Secondary exploratory analyses will examine mechanisms of change over time and the additive effect of the optional modules compared to core modules.

The embedded process evaluation will evaluate implementation, effectiveness and potential sustainability of core and optional modules through mixed methods, including surveys, programme monitoring, staff debrief meetings and qualitative interviews and focus groups. Qualitative activities will be conducted post-intervention (T2) with families who complete and drop out of the intervention, facilitators, outreach staff and other key personnel.

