## Discussion

This study aims to demonstrate the impact of an integrated approach to family mental health support for displaced and vulnerable families. It tests both upstream family mechanisms and direct impacts on adolescent mental health, providing evidence for family-systemic intervention pathways. The results will contribute to the evidence base on whole-family mental health interventions in humanitarian settings, an area currently characterised by substantial gaps, despite promising findings from caregiver-focused programmes (Giusto et al., 2025). Such integrated approaches could promote sustainability and scale in humanitarian and low-resource settings (Troup et al., 2021).

Study strengths include rigorous evidence on interventions addressing social determinants of mental health through inclusion of both displaced and host populations, use of non-specialist facilitators following task-sharing approaches (Raviola et al., 2019; Cohen and Yaeger, 2021) and modular design tailoring to family-specific needs (Kazdin, 2019).

Limitations include the complexity of measuring change in multiple outcomes over time through the sequential dual outcomes approach. While our sample size provides adequate power for testing H1 (upstream mechanisms), we acknowledge that H2 and H3 are positioned as exploratory analyses. Findings from these exploratory analyses will inform future adequately powered mechanistic studies. Additionally, while the intervention addresses multiple family stressors, some structural challenges facing refugee populations will lie beyond the intervention’s scope. Finally, we will use caregiver-report of child mental health challenges for the screening, as this is most feasible in real-world settings. While this approach has been validated in other Arabic-speaking populations (Ababneh and Alomari, 2016; Emam et al., 2016), adult proxy-report of the SDQ could result in underreporting of internalising symptoms compared to adolescent self-report. Nonetheless, adolescent-report SDQ will serve as the primary, upstream effectiveness outcome and both adolescent- and caregiver-report SDQ will be measured at all time points. Research assistants are also trained to report observations and disclosures of severe mental health and protection concerns as part of consent, screening and all rounds of data collection, ensuring referral to specialist support for respondents and their families.

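### The sample size is said to be powered for the dual outcomes approach, but the calculation shown covers H1 only, and H2 and H3 are called exploratory yet count as routes to effectiveness

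*Protocol article*

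**What the plan says.** All references are to the protocol article.

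- **Sample size** opens with "The sample size calculation was powered for the sequential dual outcomes approach". The calculation that follows is "for any of the three upstream primary outcomes (family functioning, parenting practices or caregiver mental health"), with these inputs: "Assuming a statistical significance level of 5% with an intra-cluster correlation coefficient of 0.02" and "a two-tailed test with 0.85 power". The effect is d = 0.15, and the result is 440 index adolescents and 440 caregivers, 220 per group. The recruitment target is 550 to 600.
- **Primary effectiveness hypotheses** lists H1, H2 and H3 under that one heading and presents them as the way effectiveness will be shown. It then says that the study is powered at 0.85 for H1, and that "H2 and H3 are positioned as exploratory analyses, given limitations regarding sample size".
- **Abstract** gives two components of effectiveness: upstream improvement, and adolescent improvement among those with elevated baseline distress.
- **Trial design** gives three pathways for establishing effectiveness, joined by "or". The second is "direct improvements in mental health in high-distress adolescents" and the third is the moderation effect (H3).
- **Table 3** labels the adolescent-reported SDQ as the primary downstream outcome.
- **Effectiveness analyses** places the dual outcome tests under the primary analyses. Each step is tested at p < 0.05, and the analyses continue whatever the preceding step shows.
- **Discussion** repeats that power is adequate for H1 and that H2 and H3 are exploratory.

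**The concern.** Two descriptions of the same tests stand side by side. In one, the trial is sized for a dual approach and H2 and H3 can each establish effectiveness. In the other, only H1 is powered and H2 and H3 are exploratory. No later analysis plan can satisfy both.

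What is at stake is mainly how a positive H2 or H3 would be used. If H1 fails and H2 reaches p < 0.05, Trial design allows the conclusion that effectiveness is established, while the hypotheses section and the Discussion allow only a finding to be followed up. If that choice is made after the results are known, an exploratory result can be presented as confirmatory. The opening sentence of the Sample size section would lend it a claim of power that no calculation in the article supports.

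**Working it through.** **1. What the power claim covers.** The dual outcomes approach, as the Abstract and Trial design define it, has an upstream part (H1) and an adolescent part in the high-distress subgroup (H2). Trial design adds H3. The inputs in the Sample size section are alpha 0.05 two-sided, power 0.85, ICC 0.02 and d = 0.15, tied to the three upstream outcomes. The visible text gives no SDQ effect, subgroup size or power for H2 or H3. The opening sentence therefore claims more than the calculation covers.

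**2. Role of H2 and H3, section by section.**

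| Section | Role given |
|---|---|
| Abstract | H2 is part of how effectiveness is evaluated |
| Primary effectiveness hypotheses (heading and lead-in) | H2 and H3 are primary and demonstrate effectiveness |
| Primary effectiveness hypotheses (closing text) | H2 and H3 are exploratory because of sample size |
| Trial design | H2 or H3 can establish effectiveness |
| Table 3 | Adolescent SDQ is a primary outcome |
| Effectiveness analyses | Dual outcomes are primary analyses, 0.05 per step, no gate |
| Discussion | H2 and H3 are exploratory |

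The exploratory label and the role of an alternative route to effectiveness cannot both hold.

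**3. The plan's own figures.** The attrition step reproduces: 440 / (1 − 0.20) = 550. The 220 per group does not. For a simple two-group comparison, with d in SD units:

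n per arm = 2 × (1.960 + 1.036)² / 0.15² = 799 after rounding up.

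Power at 220 per arm is Φ(0.15 / √(2/220) − 1.960) = Φ(1.573 − 1.960) = 0.35, against 0.85 stated. A one-sided test needs 640 per arm. A design effect of 1 + (m − 1) × 0.02 with m = 2 to 6 raises the two-sided requirement to about 814 to 878. A figure near 220 appears only under assumptions that the article does not state, such as a baseline-outcome correlation of about 0.85 (222 per arm). This matters here only because the repair should not restate 0.85 as achieved.

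**4. Illustration for H2.** The high-distress share is not stated. It can be below 100%, because the eligibility criteria admit families on caregiver distress without child distress. Assume shares of 30%, 50% and 70% of 440 analysed adolescents, 1:1 allocation, and a baseline-outcome correlation r of 0 or 0.7. The detectable effect with 0.85 power is

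d = (1.960 + 1.036) × √(4(1 − r²)/n).

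| Share (assumed) | n | d, r = 0 | d, r = 0.7 |
|---|---|---|---|
| 30% | 132 | 0.52 | 0.37 |
| 50% | 220 | 0.40 | 0.29 |
| 70% | 308 | 0.34 | 0.24 |

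**The case against.** The strongest reply is that the article already discloses the position. The exploratory status appears under the very heading that calls the hypotheses primary, and again in the Discussion. The second sentence of the Sample size section names only upstream outcomes. This stands, and it limits the seriousness. It does not remove the conflict, because Trial design and the analysis section still give H2 and H3 a deciding role.

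A second reply is that the article is condensed and that the footnote to the recruitment target is not shown, so power for H2 may be described elsewhere. That is also fair. The absence of a figure for H2 is not itself the fault. The fault is a power claim that the article's own later statements withdraw.

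Some stronger readings are tempting, but the documents do not support them:

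- *That H2 falls short of d = 0.15.* That effect is stated for the upstream outcomes in the full sample. No target effect is stated for H2, so there is no shortfall to measure.
- *That a null H2 would be taken as a powered negative result.* A reader would have to overlook the article's explicit statements to the contrary.
- *That nothing is left for the sub-analyses* ("as well as sub-analyses based on family composition and uptake of advanced modules"). This is so only at 550. The target runs to 600, and 600 × 0.80 = 480, which is 40 above 440. The article also does not claim that those sub-analyses are powered.
- *That the Discussion changes the role of the SDQ* ("adolescent-report SDQ will serve as the primary, upstream effectiveness outcome"). Against Table 3 this is a slip in one word, separate from the power question.

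**Conclusion.** The point holds as an inconsistency in the power claim and in the roles of H2 and H3. It rests on the text alone and does not depend on any calculation. The Sample size section claims power for an approach of which only the H1 part was calculated. Analyses declared exploratory can, as Trial design and Effectiveness analyses are written, establish effectiveness at 0.05 without a gate.

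The size for H2 can only be illustrated: detectable effects of about d = 0.52 to 0.34 unadjusted, or 0.37 to 0.24 with a correlation of 0.7. These rest on an assumed 30% to 70% share and 440 analysed adolescents. They are consistent with the exploratory label.

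A reader might infer that correcting the sentence leaves H1 securely powered. The documents do not support that either: on the stated inputs, a simple comparison at 220 per group has about 35% power for d = 0.15. Whether an unstated feature of the H1 calculation explains the difference is a separate question.

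The inconsistency should be corrected. Because it is already partly disclosed, it is moderate rather than serious.

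**What to change.** 1. In Sample size, replace the opening sentence with a statement that the calculation addresses H1 only. Do not repeat there that 0.85 power is achieved unless the inputs that give 220 per group are also stated.
2. Make the roles of H2 and H3 the same in the Abstract, Primary effectiveness hypotheses, Trial design, Table 3 and Effectiveness analyses, and do so before outcome data exist. Recruitment was due to begin in December 2025.
   - The simplest version, which matches the closing text of the hypotheses section and the Discussion, is that H2 and H3 are exploratory and cannot by themselves establish effectiveness. The adolescent SDQ then loses its primary label or is marked as exploratory.
   - If the sponsor wants to keep H2 and H3 as effectiveness pathways, the exploratory label must go, and the plan must state an error-control rule across the pathways and the power that each has.

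The cost is that the stated power claim and the success rule become less favourable to the trial. Under the first version, this narrows what can establish effectiveness, so it is a decision about the success rule as well as an edit. No extra families are needed.

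### The stated inputs (two-sided 5%, 85% power, d = 0.15) need about 798 per arm, not 220, so the power claim for H1 is not supported as written

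*Protocol article*

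**What the plan says.** The Sample size section gives the inputs and the result in one sentence. It assumes a 5% significance level "with an intra-cluster correlation coefficient of 0.02 and a two-tailed test with 0.85 power", and concludes that "440 index adolescents and 440 caregivers is required (220 per group) to detect a minimum effect size of" a specified magnitude. That magnitude is a standardised difference, d, which the section puts at 0.15 and applies to any of the upstream primary outcomes. It then allows for 20% attrition and sets a recruitment target of 550 to 600 families.

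The section on primary effectiveness hypotheses builds on this: "The study is fully powered to test H1 (power = 0.85"). It defines H1 as success on at least one of family functioning, parenting practices and caregiver mental health at endline (T2), and calls H2 and H3 exploratory. The Discussion again describes the power for H1 as adequate.

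The Statistical analysis section lists baseline measures among the fixed effects of the planned model. No baseline-to-endline correlation is given anywhere as an input to the sample size, and neither the unit nor the size of the cluster behind the ICC is stated.

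**The concern.** An effect of d = 0.15 is small, and 220 per group is far below what such an effect usually needs at 85% power. H1 is the only hypothesis for which the article claims full power, so the trial's confirmatory claim rests on this sentence. If the figures are inconsistent, readers will credit the trial with sensitivity to an effect that it may well miss, and a null result on H1 could be taken as stronger evidence against a 0.15 effect than it is.

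**Working it through.** **Inputs, all from the Sample size section:** two-sided alpha 0.05 (z = 1.960), power 0.85 (z = 1.036), d = 0.15 (SD = 1), 220 per group, ICC 0.02, attrition 20%. Allocation is 1:1 (Trial design). Each primary upstream outcome has one type of reporter: the adolescent for SCORE-15, the caregiver for the parenting scale and the K10.

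**1. The plan's own figures.**
- Attrition: 440 / 0.8 = 550. This reproduces.
- Sample size: n per arm = 2(1.960 + 1.036)² / 0.15² ≈ 798, or 799 rounded up. The stated 220 does not reproduce; 798 / 220 ≈ 3.6.

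**2. Power on one outcome with 220 per arm.** The standard error of the standardised difference is √(2/220) = 0.0953, so the expected z is 0.15 / 0.0953 = 1.573. With baseline adjustment at correlation r, the standard error is multiplied by √(1 − r²).

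| r | Power at d = 0.15 | d detectable at 85% power |
|---|---|---|
| 0 | 35% | 2.996 × 0.0953 = 0.286 |
| 0.5 | 44% | 0.286 × 0.866 = 0.247 |
| 0.7 | 59% | 0.286 × 0.714 = 0.204 |

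The correlation needed for 85% power is r = √(1 − 220/798) ≈ 0.85.

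The ICC can only reduce these powers. At r = 0, a design effect of 1.02 gives 34.4% and one of 1.10 gives 32.3%. Both design effects are assumptions, because no cluster size is stated.

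With Bonferroni control over three outcomes, the detectable effect at 85% power is 0.327 (r = 0) or 0.283 (r = 0.5).

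**3. Other ways to reach 85% on one outcome (r = 0).**
- All 550 or 600 recruited families analysed without loss: 42% or 45%.
- A one-sided test: 47%.
- All 880 respondents counted as independent: 60%. This would not suit outcomes with one type of reporter each.

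**4. Power for at least one of three outcomes.** Assume that all three outcomes shift by 0.15, with no design effect. For uncorrelated outcomes, power is 1 − (1 − p)³, where p is the power on one outcome. For correlated outcomes it was simulated from a trivariate normal distribution.
- r = 0, unadjusted 5%: 1 − (1 − 0.349)³ ≈ 72% if uncorrelated, 65% at outcome correlation 0.3, 59% at 0.5.
- r = 0.55, unadjusted 5%, uncorrelated: the expected z is 1.573 / √(1 − 0.55²) = 1.884, so p ≈ 0.470 and power ≈ 85%.
- r = 0.7, unadjusted 5%, outcome correlation 0.3: 87.5%.
- r = 0.5, Bonferroni: 63% if uncorrelated, 51% at outcome correlation 0.5.
- r = 0.75, Bonferroni, uncorrelated: 87%.

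At an unadjusted 5% per outcome, the chance of at least one false positive is 1 − 0.95³ ≈ 14% if uncorrelated, and 13.6% at outcome correlation 0.3.

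**The case against.** The strongest defence is that H1 needs success on only one of three outcomes, so the 0.85 may be the power for at least one success, and that the planned model adjusts for baseline. Both points have force. The phrase on any of the three outcomes can be read either way, and the 35% figure is a floor that applies to one outcome without baseline adjustment and before any design effect.

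For that reason several stronger readings should be resisted.

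- A reader might infer that the trial would miss a 0.15 effect about two times in three. That holds only for one outcome at r = 0. The miss rate is 56% at r = 0.5 and 41% at r = 0.7.
- A reader might infer that the power claim for H1 is proved false. The documents show only that the stated inputs do not support it, since step 4 gives combinations that reach 85%.
- A reader might infer that those combinations require uncorrelated outcomes or no multiplicity control. They do not: 87.5% is reached at outcome correlation 0.3, and 87% with Bonferroni. In these calculations, however, every route assumes effects on all three outcomes and a baseline correlation of at least about 0.55. Neither assumption is stated.
- A reader might conclude that 0.15 was Cohen's f, which equals d = 0.30. It is true that d = 0.30 needs 199.5 per arm, and 199.5 × 1.10 = 219.5. But the article does not mention f, and the design effect of 1.10 was chosen because it lands on 220. This is only a possibility for the authors to check.

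It could also be said that an article condenses the full protocol, that the earlier trials cited as the basis are not shown, and that a footnote in this section is not visible. The footnote is attached to the recruitment target, not to the effect size. The point is not that detail is absent: alpha, sidedness, power, effect size and sample size are given together as one calculation, and they do not agree.

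**Conclusion.** The point holds. Taken as stated, the inputs require about 798 per arm, and 220 per arm gives 35% to 59% power on one outcome at d = 0.15 for baseline correlations from 0 to 0.7. The effect detectable at 85% power is about 0.29 to 0.20 over the same range, and larger with multiplicity control. If power means success on at least one of three outcomes at unadjusted 5%, it is about 59% to 72% without baseline adjustment (outcome correlation 0.5 to 0). It reaches 85% only with additional unstated assumptions. On the unadjusted routes shown, the chance of at least one false positive is then about 13% to 14%.

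These results assume a comparison of means at T2 with 440 families analysed. The tabulated figures carry no design effect, so they are slightly favourable to the plan. The values of r and of the outcome correlation are assumptions shown as ranges.

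**What to change.** Correct the Sample size section, and align the power statement under the primary effectiveness hypotheses and the one in the Discussion. Either of two restatements would do:

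- give the effect that 440 analysed families can detect at 85% power: about d = 0.29, or about 0.25 if a baseline correlation of 0.5 is assumed, with the larger figure that follows from whatever multiplicity rule is adopted for H1; or
- keep d = 0.15 and state the power that 440 analysed families give for it.

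In both cases, state the assumed baseline-to-endline correlation, the cluster unit and cluster size behind the ICC of 0.02, and whether the power is per outcome or for at least one of three. The authors should also check whether 0.15 was entered as Cohen's f and, if so, report it as d = 0.30.

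The cost is a change of wording and a less favourable stated figure. If 0.15 is truly the smallest effect of interest, restating the figures will not make the design able to detect it with 85% power, and the authors would need to say how they weigh that.
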